#### Loneliness

The De Jong Gierveld Short Scale for emotional and social loneliness, a 6-item self-report measure will be used [71]. Patients answer three questions about social loneliness, characterized by a smaller number of friends than is considered desirable, and three questions about emotional loneliness, characterized by a lack of intimacy in current relationships, on a 6-point scale. The sum of both subscales indicates overall loneliness. The Dutch version of this short form has good psychometric properties [71].

#### Therapeutic alliance

To measure therapeutic alliance, the Session Rating Scale (SRS) is the instrument of choice. It consists of 4 visual analogue scales and aims to measure the self-reported therapeutic alliance by the patient [72]. The psychometric properties of this instrument are satisfactory and the feasibility in clinical practice is found to be good [72].

#### Psychomotor performance

With the Digit Symbol Substitution Test (DSST) the degeneration or improvement of psychomotor performance can be measured [73]. The DSST is pencil and paper test in which the patient is given a combination of numbers and matching symbols and a test section with numbers and empty boxes. The patient is asked to fill as many empty boxes as possible with a symbol matching each number within 90 s.

#### Executive functioning

To measure whether behavioural activation is effective regardless of the level of executive functioning of the patient, the Stroop-task will be used [74, 75]. Patients will be presented with three different sheets of words and/or colours. The first sheet contains colour names in black ink. Patients are asked to read the colour names. The second sheet consists of squares printed in different colours. Patients are asked to name the colours on the sheet. The last sheet contains the words “red”, “green” and “blue” that are printed in sometimes the same (e.g. the word red in red ink) and sometimes a different colour ink. The task is to name the colour of the ink in which the word is printed as quickly as possible. The increase in time taken to perform the latter task compared with the basic task is referred to as “the Stroop interference effect”.

#### Treatment expectations

To asses treatment expectations, the credibility & expectancy questionnaire will be used [76]. The questionnaire consists of six questions that are assessed on a 9 point Likert-scale. The questionnaire appears to have high internal consistency within each factor and good test–retest reliability [77]. Expectancy measures will not be used to ensure initial equivalence between two compared treatments, but to measure individual differences in expectancy within the BA group.

### Sample size

Comparing the effects BA for depression to a waiting list condition, Cuijpers et al. reported an effect size of 0.9 in a meta-analysis [27]. Since we will be comparing BA to a more active treatment condition (TAU) in depressed older patients, we estimate the effect size for depression outcome of BA versus TAU to be 0.50, a modest but clinically relevant value. Based on this estimate (alpha = 0.05, power (beta) = 0.80, 2-tailed test) and data clustering within PCCs (ICC of 0.05 and a cluster size of *n* = 6) 100 patients are required per group with two groups of 14 clusters (based on 14 potential patients per PCC and a 50% refusal and a 20% dropout rate).

### Recruitment

Several general practices in the South-Eastern region of the Netherlands are recruited to participate in the study. General practitioners and mental health nurses are responsible of the recruitment of participants.

### Assignment of interventions

PCCs are the units of randomization. PCCs that employ the same MHN will be in the same treatment condition, preventing contamination. An independent statistician will use pairwise matching to randomize the PCCs, taking into account the amount of MHNs in a PCC, as well as the sex of the MHN and the size of the patient population. In half of the PCCs the MHNs are trained to give BA-treatment while the other half will treat patients as usual. GPs, patients and MHNs are not blinded to treatment condition because PCCs are the units of randomisation, but the research assistants that assess depression after treatment are blind to condition.

### Data management

Data are handled confidentially as each patient is coded with a number. The link between the patient code and patient information is preserved in a digital document that will be protected by a password. This document is only available to the principal investigator, the executive researcher and the two research assistants. Coded patient data are kept in a folder that is stored within a different section of the RadboudUMC database than the source data. Informed consent forms are kept in a locked closet, separated from the paper and pencil questionnaires that also will be archived in a locked closet. Digital data are stored in Castor EDC, a program with a built in audit trail. Patients will send the filled in questionnaires by mail or e-mail. A research assistant will call patients when there is missing information in a questionnaire, or when a questionnaire is not returned in time. When a patient does not want to continue in the study, all the information up until then is used in the analyses but no additional information is collected.

### Statistical analyses

#### Clinical outcomes

Data analyses include intention-to-treat analyses and per-protocol analyses. The relative effectiveness of behavioural activation and treatment as usual will be analysed using mixed linear regression modelling. In addition, we will determine the proportion of patients that show reliable and clinically significant improvement on the outcome measures, based on the model of Jacobson and Truax [78, 79]. Relapse (episode of MDD after remission) and recurrence (episode of MDD after recovery) will be assessed in the course of follow-up (6, and 12 months) using survival analysis (Cox proportional hazards regression). Intention to treat analyses as well as per protocol analyses will be conducted.

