**Fig. 1 Fig1:**
[figure not shown]
Theoretical framework for potential mechanisms of action

The following main research questions were formulated:What is the effectiveness of BA compared to TAU for older adults with clinically relevant depressive symptoms over the course of 12 months?What is the cost-effectiveness of BA compared to TAU from a societal perspective for older adults with clinically relevant depressive symptoms, over the course of 12 months?What are the mechanisms of change that account for the effectiveness of BA compared to TAU?What are the predictors and moderators of outcome of BA compared to TAU?

In line with previous research, we hypothesize that BA is more effective and cost-effective than TAU [21–31].

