### Eligibility criteria

General practitioners and mental health nurses are responsible of the recruitment of participants. They include eligible patients during consultations (see procedures for details). We will include 200 older adults (≥65 years). All patients presenting with depressive symptoms or depression are asked to participate. Those who have a PHQ-9 score > 9 and have given informed consent will be included in the study. Patients will be excluded from the trial in the case of 1) current severe mental illness in need of specialized treatment, including bipolar disorder, obsessive-compulsive disorder, (history of) psychosis, high risk of suicide, drug and/or alcohol abuse, 2) psychotherapy in the previous 12 weeks or current treatment by a mental health specialist and 3) moderate to severe cognitive impairment. Patients with antidepressants are eligible provided that a stable dose has been maintained for at least 12 weeks before participating in the study.

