In the follow-up period (3 to 12 months after baseline), patients will receive a follow-up questionnaire every three months. After twelve months the last follow-up home-visit by a research assistant will be planned.

For a detailed schedule of all measurements per time-point, see Table 1.

**Table 1 Tab1:** Participant timeline

		Treatment phase (weekly)									Follow up (3 monthly)			
Measures^a^	-1	0	1	2	3	4	5	6	7	8	3	6	9	12
Clinical outcome measures														
Depression (PHQ-9)^b^		•	•	•	•	•	•	•	•	•	•	•	•	•
Mini 5.0 (2 questions)	•													
MINI 5.0 interview (baseline complete, T8 only depression)		•								•				
Cognitive (MoCA)		•												•
Depression (QID-S)		•								•	•	•	•	•
Well- being & mood^c^ (visual analogue scale)			•	•	•	•	•	•	•	•				
Psychopathology *(BSI-SF)*		•								•				•
Limitations (WHODAS)		•								•				•
Process BA-specific														
Behavioural activity (BADS)		•		•		•				•	•	•	•	•
Physical activity (accelerometer)		•								•				
Ruminative brooding (RRS)		•		•		•				•	•	•	•	•
Process general														
Loneliness (S&ES)		•				•				•	•	•	•	•
Therapeutic alliance (SRS)^c^			•	•	•	•	•	•	•	•				
Cognitive (STROOP & DSST)		•								•				•
Expectancy (Expectancy and credibility list)^c^		•												
Cost effectiveness														
TIC-P		•									•	•	•	•
EQ-5D		•								•	•	•	•	•

^a^− 1 = screening by GP, 0 = baseline measurement by research assistant, 8 = post-treatment measurement by research assistant ^b^administered weekly in BA and two-weekly in TAU. ^c^only administered in BA

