#### Depressive disorder and psychiatric comorbidity

To distinguish patients with a major depressive disorder (MDD) from patients with only clinically relevant symptoms a research assistant will administer the complete Mini International Neuropsychiatric Interview (M.I.N.I. 5.0.0). Furthermore, this instrument assesses psychiatric co-morbidity. The M.I.N.I. 5.0.0 is a short diagnostic interview that assesses current psychological disorders, based on DSM-IV diagnostic criteria. The reliability and validity of the M.I.N.I are good [49]. The M.I.N.I. can be administered in about 15 min [53].

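### Relapse and recurrence carry an intention-to-treat label, but only patients who remit or recover after randomisation can have these events, so a BA v TAU hazard ratio is not a randomised comparison

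*Protocol article*

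**What the plan says.** Five statements in the protocol article bear on this.

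- **Event and method** (Statistical analyses, Clinical outcomes): "Relapse (episode of MDD after remission) and recurrence (episode of MDD after recovery) will be assessed in the course of follow-up", at "6, and 12 months) using survival analysis (Cox proportional hazards regression".
- **Analysis sets** (same paragraph, next sentence): "Intention to treat analyses as well as per protocol analyses will be conducted".
- **Unit of allocation** (Assignment of interventions): "PCCs are the units of randomization".
- **Entry** (Eligibility criteria): "Those who have a PHQ-9 score > 9 and have given informed consent will be included in the study". MDD is not required. The M.I.N.I. is used "To distinguish patients with a major depressive disorder (MDD) from patients with only clinically relevant symptoms".
- **Expected direction** (Objectives and hypotheses): "we hypothesize that BA is more effective and cost-effective than TAU".

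The Clinical outcomes paragraph opens with the relative effectiveness of BA and TAU, analysed by mixed linear regression. It does not write out the Cox model's risk set, time origin or treatment term.

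**The concern.** An episode of MDD after remission presupposes remission, and recurrence presupposes recovery. Both states arise after allocation, and both are what BA is meant to bring about. Suppose BA brings additional, harder-to-treat patients to remission. Its remitters then have a worse average prognosis than the fewer remitters under TAU, and their relapse rate can be higher although BA causes no relapse. Patients who entered without MDD have no MDD to remit from, which narrows the set further.

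At stake is how a secondary result is read. A hazard ratio reported under an intention-to-treat label would be taken as randomised evidence on whether gains last. It would not have that protection, even if MDD were ascertained perfectly throughout follow-up.

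**Working it through.** **1. The plan's own figure.** The only stated sample size is 100 per group, for the depression outcome (Sample size section).
- n per arm = 2 × (1.96 + 0.84)² / 0.50² ≈ 63
- Design effect = 1 + (6 − 1) × 0.05 = 1.25, giving 63 × 1.25 = 78.75, so 79
- Dropout: 79 / 0.80 = 98.75, so 99, against 100 stated

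The figure reproduces, so the point does not rest on a sample-size error. Nothing is stated for relapse or recurrence.

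**2. Arithmetic by type of patient.** All rates here are assumptions. Let remission be 35% under TAU and 50% under BA. Let relapse be 20% in patients who would remit in either arm and 40% in those who remit only because of BA. BA harms no one.
- Relapse among TAU remitters: 20.0%
- Relapse among BA remitters: (0.35 × 0.20 + 0.15 × 0.40) / 0.50 = 26.0%
- Approximate hazard ratio: ln(1 − 0.26) / ln(1 − 0.20) = 1.35, against BA
- Sustained remission among all patients: TAU 0.35 × 0.80 = 28.0%; BA 0.50 × 0.74 = 37.0%, in favour of BA

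If the extra remitters have the same relapse risk as the others, the ratio is 1.00. With an extreme choice (remission 30% v 50%, extra remitters' risk 50%), BA relapse is (0.30 × 0.20 + 0.20 × 0.50) / 0.50 = 32% and the ratio is 1.73.

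If BA truly lowers relapse risk by 20% in the 35% v 50% example, BA relapse is 0.8 × 26.0% = 20.8% and the ratio is ln(0.792) / ln(0.80) = 1.05, so the benefit is hidden. With a common risk of 30%, the same reduction shows as ln(0.76) / ln(0.70) = 0.77.

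**3. Simulation.** One million patients per scenario share a normally distributed prognostic factor that acts on both remission and relapse. The relapse hazard is 0.4 per year at the average value of the factor, follow-up is 0.83 years, and BA has no effect on relapse. The coefficient of the prognostic factor is 0.5 (moderate) or 1.0 (strong). Repeat runs agree within about 0.02.

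| Remission BA v TAU | Relapse rate ratio BA:TAU, moderate to strong |
|---|---|
| 50% v 50% (control) | 1.00 |
| 50% v 35% | 1.05 to 1.21 |
| 60% v 40% | 1.07 to 1.25 |
| 60% v 30% | 1.11 to 1.43 |

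A second simulation shifts remission by the protocol's d = 0.50. With remission of 35% under TAU and 55% under BA it gives 1.00, 1.07, 1.15 and 1.26 as the link between vulnerability and relapse rises from none to a log hazard ratio of 1.0 per SD. Sustained remission among all patients favours BA each time (28.4% v 42.8% where the ratio is 1.15).

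**4. Precision.** Assume that the MDD share among trial patients equals the ratio of the major and minor depression prevalences in the Background: 13.7 / (13.7 + 10.2) = 57%. Those are prevalences in elderly primary care patients, not in patients with PHQ-9 > 9, so the share is only a rough guide.
- With 80 retained per arm: 80 × 0.573 ≈ 46 with MDD
- With remission 60% v 40%: 46 × 0.6 ≈ 27 and 46 × 0.4 ≈ 18 at risk
- Relapse risk, ignoring the prognostic factor: 1 − exp(−0.4 × 0.83) = 28%, so about 7.6 and 5.1 events
- SE of the log hazard ratio: √(1/7.6 + 1/5.1) ≈ 0.57; 95% limits at a factor of exp(1.96 × 0.57) ≈ 3 either way, before clustering
- Largest bias in this scenario: ln(1.25) = 0.22, about 0.4 SE

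**The case against.** - **The comparison is inferred.** The article names events and a method but no risk set or treatment term, and a fuller protocol or SAP may supply them. This stands in part: it is too strong to say that no intention-to-treat set could be built. But the event definitions are fixed here, and a Cox model in a two-arm effectiveness paragraph followed by intention-to-treat wording is most naturally read as a contrast between arms. A SAP that keeps the definitions keeps the problem.
- **Durability is already covered.** This stands. A reader might infer that the trial's evidence on lasting benefit is compromised. The documents do not support that. The primary outcome, QIDS-SR, is scheduled in both arms at post-treatment and at 3, 6, 9 and 12 months, and its mixed model does not condition on remission. Nor do the planned proportions with reliable and clinically significant improvement.
- **The bias is assumed, may be nil, and is smaller than the noise.** This stands. A reader might infer that an effective BA will look harmful. The working shows only that it may, and a real protective effect can still appear.
- **The endpoint must be redefined anyway.** Table 1 lists "MINI 5.0 interview (baseline complete, T8 only depression" at baseline and week 8 only, with no later M.I.N.I. That is a separate matter of ascertainment. Settling it would not remove the selection described here, though both could be handled in one revision.

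**Conclusion.** The point holds as a limit on interpretation of a secondary analysis. Followed as written, relapse and recurrence are assessed in a group formed after allocation by the process that BA is expected to change, so a BA v TAU hazard ratio there is not protected by randomisation, whatever the label.

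With no BA effect on relapse, the simulated ratio runs from 1.00 to about 1.4; only more extreme inputs in the simple arithmetic go beyond that. All remission rates, relapse rates and prognostic strengths are assumptions, as is the 57% MDD share. With about 27 v 18 patients at risk, random error would outweigh the bias, so the ratio could neither establish durability nor reveal its own distortion. The primary QIDS-SR analysis is untouched, which keeps this at the level of a recommended correction.

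**What to change.** In the Clinical outcomes paragraph:

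1. State that relapse and recurrence among patients who have remitted or recovered are reported descriptively by arm and are not intention-to-treat comparisons.
2. Add a secondary endpoint that every included patient can have, analysed by the allocation of the practice. Two options are remission status on the QIDS-SR at each visit, or sustained remission with never-remitters counted as failures.
3. For that endpoint, fix in advance the QIDS-SR cut-off (the article gives none), a rule for missed visits (20% dropout is expected), the handling of patients who first remit after post-treatment and of those already below the cut-off at baseline (entry is on the PHQ-9), and allowance for clustering by practice.

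**Cost.** No new data are needed, because the QIDS-SR is already scheduled at all these visits in both arms. The work lies in the wording and in the rules under item 3. Two things are given up. Relapse hazard ratios are no longer offered as comparative evidence. The added endpoint combines reaching and keeping remission, on a self-report scale completed by unblinded patients, so it answers a different question from MDD episodes.

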### Procedure

Older adults that visit their GP with depressive symptoms, complaints of loneliness, reduced social functioning, medically unexplained symptoms, and/or frequent attenders without a clear somatic diagnosis will be screened for potential eligibility. If the GP or MHN suspects depressive symptoms or if the patient fulfils one of the aforementioned criteria, the GP or MHN will screen the patient with the first two questions of Mini International Neuropsychiatric Interview (M.I.N.I. 5.0.0.) [49] on depressive symptoms. If one or both of the questions is answered affirmatively, the GP will provide the patient with basic information about the study and will ask whether (s)he agrees to be contacted by our research assistant.

Eligible participants receive a letter with study information and are contacted by a research assistant to plan a baseline visit, that takes place approximately one week after they’ve received the letter. This will allow them to make an informed decision about their participation. At the baseline visit a research assistant will visit the patient at home to assess whether (s)he fulfils the inclusion criteria and is willing to participate. During this visit, also several cognitive tests will be performed, and the presence of depressive disorder will be established with a semi-structured clinical interview M.I.N.I. 5.0.0 [49]. After the baseline meeting, the patient will receive the online or paper-pencil baseline questionnaire, which they will be asked to complete within the following week. Furthermore, the patient will wear an accelerometer for one week. Approximately one week after the baseline meeting the BA- or TAU-treatment is started.

During the treatment phase (baseline to 9 weeks), patients in both research conditions will receive a questionnaire every two to four weeks at home. BA patients also fill in a short questionnaire during the weekly sessions with the MHN. Nine weeks after the baseline assessment, patients will receive a call from a research assistant for the post-treatment assessment consisting of two cognitive tests, as well as a short interview to establish the presence of depressive disorder. After this, patients will wear the accelerometer for another week, and complete the post-treatment questionnaire within that week.

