## Outcomes

### Clinical outcome measures

#### Depressive symptoms

The Quick Inventory of Depressive Symptomatology (QIDS-SR) will be used as the primary outcome measure of depressive severity. The QIDS-SR is a 16-item self-report instrument assessing depressive symptoms during the last two weeks. It can be administered in 5–7 min and has good psychometric properties [48].

The Patient Health Questionnaire- 9 (PHQ-9) is a 9-item self-report instrument assessing depressive symptoms during the last week. It will be used as a secondary outcome measure and to assess changes in depressive symptoms over the course of treatment. The psychometric properties of the PHQ-9 are good [50, 51]. Patients scoring PHQ-9 > 9 are classified as having clinically relevant depressive symptoms [52].

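### Relapse and recurrence are defined as MDD episodes at 6 and 12 months, but no MDD diagnosis is scheduled after post-treatment, so this secondary outcome cannot be derived as defined

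*Protocol article*

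**What the plan says.** Under Statistical analyses, Clinical outcomes, the article defines two events in terms of a diagnosis. The first is "Relapse (episode of MDD after remission"), and the second follows in the same sentence: "recurrence (episode of MDD after recovery) will be assessed in the course of follow-up (6, and 12 months) using survival analysis", with Cox proportional hazards regression named as the method.

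The section on depressive disorder and psychiatric comorbidity names the M.I.N.I. as the instrument that establishes MDD (the quote stops partway through its full name): "To distinguish patients with a major depressive disorder (MDD) from patients with only clinically relevant symptoms a research assistant will administer the complete Mini International".

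The Procedure section introduces its timeline as complete: "For a detailed schedule of all measurements per time-point, see Table 1". The diagnostic row of that table reads "MINI 5.0 interview (baseline complete, T8 only depression") and is marked at baseline and T8. The text agrees for post-treatment, where the telephone assessment includes two cognitive tests "as well as a short interview to establish the presence of depressive disorder". For follow-up it describes three-monthly questionnaires and one visit: "After twelve months the last follow-up home-visit by a research assistant will be planned". No diagnostic interview is mentioned there.

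The primary outcome is a symptom scale: "The QIDS-SR is a 16-item self-report instrument assessing depressive symptoms during the last two weeks".

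**The concern.** The event in the planned survival analysis is a diagnosis, and the schedule makes no diagnosis in the period when the event is to be counted. If this is left as it stands, the analyst must either drop the analysis or substitute a cut-off on a self-report scale. A cut-off chosen at that stage is an event definition chosen with the data in hand, and patients who complete these scales know their treatment. The blinded interview that the Discussion offers as protection against biased judgement of MDD is described for post-treatment only.

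Two consequences follow for the analysis itself. Status known only at scheduled visits does not give the event times that a standard Cox model uses. And a relapse or recurrence can occur only in a patient who has first remitted or recovered, which happens after randomisation and may depend on treatment.

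**Working it through.** The article gives no event rate, number at risk or power for relapse, so there is no figure of the plan's to reproduce on this point. The stated 100 per group belongs to the depression score and plays no part here. It does reproduce: 64 per group for an effect of 0.50 by t-test, × [1 + (6 − 1) × 0.05] = 64 × 1.25 = 80, and 80 / (1 − 0.20) = 100.

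The check is of the analysis text against the schedule.

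**1. Reading Table 1.** It has 14 time columns: −1, 0, weeks 1 to 8, and months 3, 6, 9 and 12. The relevant rows, with two others to confirm that the columns align:

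| Row | Marked at |
|---|---|
| M.I.N.I. interview | 0, T8 |
| QIDS | 0, T8, months 3, 6, 9, 12 |
| MoCA | 0, month 12 |

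The M.I.N.I. row has 14 cells for 14 columns, and the other two rows fall where the text leads one to expect. The empty follow-up cells are therefore not an artefact of how the table was extracted. The M.I.N.I. row's own label also names only baseline and T8.

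**2. Needed against collected.**

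| Time | MDD status needed | M.I.N.I. scheduled |
|---|---|---|
| 6 months | yes | no |
| 12 months | yes | no |

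Scheduled diagnoses after T8: 0 of 4 follow-up points.

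**3. Can a scheduled scale stand in?** Not under the article's own definitions. It labels a PHQ-9 score above 9 as clinically relevant symptoms, and it uses the M.I.N.I. precisely to separate MDD from such symptoms. It gives no QIDS-SR or PHQ-9 rule for an MDD episode, for remission or for recovery.

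**4. Event times.** With status read at 6 and 12 months, an event can fall in only two intervals (T8 to 6 months, 6 to 12 months). With the QIDS-SR at 3, 6, 9 and 12 months there are four. Times are then heavily tied and interval-censored, unless onset dates are collected, and the article describes none.

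**5. What a symptom definition can see.** The QIDS-SR looks back two weeks. Four follow-up scores cover 4 × 2 = 8 weeks. From the post-treatment assessment at nine weeks to week 52 there are 52 − 9 = 43 weeks. Coverage is 8 / 43 = about 19%, so episodes that begin and end between visits would be missed.

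**6. The comparison.** By definition, the risk set is made up of patients who have remitted or recovered. Membership is determined after randomisation, so a hazard ratio between arms within it is not protected by randomisation, although the same section promises intention-to-treat analyses.

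**The case against.** **A journal article condenses the protocol, and a follow-up interview may be in the full document.** That is possible. But this is not an omitted detail: the article gives a schedule that it presents as covering all measurements, and that schedule excludes the measurement its analysis section needs. The two have to be reconciled wherever the correct statement lies.

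**The BSI-18 is scheduled at 12 months, and the article says it can detect depression according to DSM-IV.** This is true, but the scale is self-report, is absent at 6 months, and is nowhere linked to relapse. It does not close the gap.

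**Handling of ties and censoring is usually left to the analysis plan, and the 6 and 12 months may be analysis horizons.** This has some force. The choice of model is a consequence of the main problem, not a separate fault of the same weight.

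**The durability question is answered elsewhere.** This stands. A reader might infer that the trial has no valid measure of durability. It does: the QIDS-SR is collected throughout follow-up, mixed linear regression on an intention-to-treat basis is planned, and proportions with reliable and clinically significant improvement are planned too.

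**The bias among remitters might be thought to run against BA.** That would hold only if BA's additional remitters were harder to treat, and the documents say nothing on who remits. The comparison may be confounded; the direction is unknown.

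**A power figure might seem natural.** The documents supply no remission or relapse rates. Entry requires a PHQ-9 score above 9, not MDD, so the analysed sample cannot be treated as the population at risk of MDD relapse. Any such figure would rest on assumption alone.

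**Conclusion.** The point holds. Relapse and recurrence, as MDD episodes at 6 and 12 months, cannot be derived from the published schedule, because none of the four follow-up points carries the diagnostic interview. This rests on Table 1 being the complete schedule, as the article presents it.

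Severity is moderate. The outcome is secondary: it appears in one part of the analysis section, is not listed among the outcome measures, and does not enter the sample size. The primary QIDS-SR analysis is untouched. The unsuitability of standard Cox regression and the possible confounding among remitters are subsidiary points, to be dealt with in the same revision.

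**What to change.** Reconcile the Clinical outcomes text with Table 1 before analysis, by one of two routes.

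- **Symptomatic relapse.** Rename the outcome, and prespecify QIDS-SR criteria for remission and for relapse, applied to the 3, 6, 9 and 12-month scores already scheduled. Make no MDD claim.
- **MDD relapse.** If the MDD claim is kept, show the M.I.N.I. depression section in Table 1 at each follow-up point where MDD is claimed, preferably covering the time since the last contact and recording onset dates. A home visit already exists at 12 months; at 6 months only a questionnaire is planned.

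Under either route:

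- Replace standard Cox regression with a discrete-time model (for example, complementary log-log) or an interval-censored model that allows for clustering by PCC.
- Compare the arms on remission status at each follow-up in all randomised patients, for example with a mixed logistic model.
- Report relapse among remitters as descriptive.

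The first route costs wording and a change of model, with no new data. Its downside is that a symptom-based definition is less specific than a diagnostic interview and misses episodes between visits. The second route costs additional interviews, and a diagnosis not made when a visit took place cannot be recovered from the scheduled scales.
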